#### Social service utilization

Social assistance recipients’ use of social services, such as meal programs, outreach services or drop-in centres, may similarly undergo cyclical changes or face barriers to accessing services at times when these are oversubscribed. Similar to health care utilization indicators, the study instrument includes questions asking participants about social service access, barriers to accessing services and the timing of service access barriers in relation to cheque issue in the past six months (baseline) and past 2 weeks (baseline and follow-up).

#### Income and material security

Consideration of income generation is critical given that many social assistance recipients supplement their income with illegal or prohibited income generation (e.g., sex work, drug dealing) [14, 15], and that such activities are associated with health harms [14, 15, 56]. Therefore, changing assistance patterns may change patterns of other income generation. To assess the impact of the intervention on financial well being, we measure income generation activity, income amounts and material security in the past six months (baseline), and past 2 weeks (baseline and follow-up). Data referring to the past six months is collected using an instrument verified for use in the current study context [15, 58]. Data referring to the 2 weeks prior to interview is collected by expanding the use of the Timeline Followback instrument to track daily income generation information, including sources and estimated daily earnings. Material security in the past six months (baseline) and past 2 weeks (baseline and follow-up) is assessed using a validated scale [59] that has been adapted to the current study context. Further measures include involvement in acquisitive criminal activity, such as theft, as well as amounts of drug debt accumulation and to whom drug debt is owed.

#### Quality of life

To support health economic evaluation, the Canadian Euroqol Group EQ-5D [60, 61] will be administered at baseline and all follow-up visits. The EQ-5D can be administered quickly and measures health related quality of life and includes participant self-reports of mobility, self-care, usual activities, pain/discomfort and anxiety/depression, as well as a health thermometer ranking of a participant’s overall state of health, and has been validated for use among PWUD [62].

#### Study-related measures

To assess considerations related to the study and study intervention that may affect study outcomes, at baseline we collect information on individual’s motivations to participate in the study (e.g., financial compensation, desire to reduce drug use around cheque issue) and their treatment arm preference. At baseline and the final follow-up visit, participants complete the client satisfaction questionnaire (CSQ), a validated instrument [63] that assesses satisfaction with services and is used here to measure participant perceptions about social assistance receipt, including the degree to which social assistance and related Ministry of Social Development and Social Innovation supports meet needs, help with problems, and are satisfactory. Additionally, for participants that withdraw from the intervention prior to completing their 26-week intervention period, questions are asked about their reasons for and circumstances surrounding withdrawal. At the final study follow-up we assess participant experiences, including participant opinions about the benefits and drawbacks of their intervention and best options for cheque issue timing and frequency.

### Participant safety

The design of the current trial does not involve any change in the amount of social assistance provided to participants, and we therefore do not anticipate any negative changes to their financial well-being. However, desynchronizing social assistance may disrupt money management strategies, potentially interfering with the payment of expenses. Importantly, most participants in the TASA study have the rent portion of their social assistance paid directly to their landlords. Participants who have rent or other expenses can make arrangements on a case-by-case basis with Pigeon Park Savings to ensure the availability of funds at the appropriate time. Additionally, for staggered and split arm participants, receiving multiple payments per month may result in more frequent periods of intensified drug use, albeit these periods will likely be shorter or less intense given that less money will be disbursed at any one time. For intervention participants, there may also be challenges transitioning onto or off of a new social assistance payment schedule at the start or end of the study period. To mitigate this concern, study staff members can provide referrals to financial management support services as appropriate. We do not anticipate the study will expose participants to unusual risks. Nevertheless, we monitor participant safety as a part of each bi-weekly participant assessment, including considerations of food and housing insecurity, exposure to violence, access to critical health and social services and other emerging issues. We follow standard reporting procedures for adverse events and serious adverse events [64], including oversight from an external, independent Data Safety and Monitoring Committee (DSMC). Participants are able to withdraw from the intervention, the study, or both at any point, and may be withdrawn from either by investigators in the event of concerns over safety.

### Sample size

We base sample size calculations for the TASA study on an a priori minimum clinically important difference (MCID) in the rate of individuals reporting intensified drug use on government cheque issue days between control and non-control participants. For the purposes of sample size calculations, comparisons were drawn between control and staggered arm participants. We anticipate this intervention will have a lesser impact on the primary outcome of interest than the staggered and split arm and should therefore provide basis for sample size calculations. Given a lack of prior comparable experimental research, the MCID was set conservatively to a 20 % difference between control and staggered intervention arm participants. This MCID was based on results from previous observational studies that report increases in the rates of drug related harm between 24.9 and 81.2 % in the days surrounding government cheque issue [5, 7, 12, 13, 17–20, 57]. We combined this MCID with an estimate of 85 % of individuals in the control group reporting intensified substance use on community cheque issue day (*Pc*). This was set lower than 100 % to account for potential reporting biases at study screening, where all participants must indicate elevated use in order to be eligible, as well as any study participation effect on the outcome of interest among control arm participants.

Sample size calculations used methods to detect differences between proportions in a repeated measures design and were calculated using Power and Sample Size (PASS v.12) software. Sixty-five participants per arm completing all follow-ups would allow the detection of a 20 % difference in the rates of intensified drug use between control and staggered intervention arm participants with 80 % power at a 5 % significance level. These calculations assumed that control and intervention arm rates of intensified drug use follow a Bernoulli distribution, the number of government cheque issue days falling within the observation period is 6 and, as in previous studies involving PWUD [65], the autocorrelation between measures of the same individual over time *(ρ)* is 0.6. Based on previous studies among PWUD, and noting the importance of accounting for missed follow-up visits and loss to follow-up [66], we additionally account for observation-level non-response of 33 % and a potential rate of loss to follow-up of 25 %, reaching a final sample size of 91 individuals per arm or 273 in total across all three arms. The possibility of type II, false negative findings, could result from insufficient power, or, in the event of intervention withdrawal, the dilution of the effect of the intervention in ITT analyses from participants who have resumed regular synchronized payments but are analyzed as part of the intervention arm. These risks will be partially mitigated by the inclusion of sensitivity analyses, as outlined in the Data Analysis section below.

### Data linkages

To verify participant self-report wherever possible, and supplement data for the assessment of cheque issue-related costs incurred by institutions that provide social, health, financial and security (i.e., policing) services to PWUD and their communities, we will obtain third party service provision and administrative records from external databases on all participants. Participant records will be requested from hospitals, health service providers, the provincial prescription medication database, Provincial Ministry of Social Development and Social Innovation, study partner credit union, and police and criminal justice databases. Records will be requested for a 30-month period beginning 1 year before the beginning of active study participation through to 1 year after following the completion of active study participation in order to assess the impact of study involvement on access to medical and social services over time. Data linkages will be established through participant names, birth dates and participants’ personal health number, a unique and persistent identifier issued for medical billing and tracking purposes to all residents of British Columbia. Data will be de-identified to protect participant confidentiality.

### Data analysis

#### Quantitative analyses

At the conclusion of the trial, the primary and secondary endpoints will be assessed via intention-to-treat analyses [67], including all patients randomized regardless of compliance with the intervention protocol. Sub-analyses will include a modified intention-to-treat analysis that will use all participants with at least one follow-up [67, 68]. First, we will compile descriptive characteristics of the sample, assessing for systematic differences in key characteristics across study arms using the Chi-Square test for binary variables and the Mann-Whitney *U* test for continuous variables. The primary outcome of interest will be derived from TLFB information as a repeated binary variable (intensified drug use on the 3 days beginning with government cheque issue day vs. not) and will be quantified as the proportion of individuals TASA participants reporting increased drug use during this period at each government cheque issue. This outcome, and other secondary outcomes similarly quantified will be examined using pooled generalized linear mixed effects models, with binomial distribution and logit link specified to produce unadjusted and adjusted odds ratios and 95 % confidence intervals. Other secondary outcomes of interest, quantified as counts of the number of occurrences over the course of the observation period (e.g., hospital ED admissions), will be examined using generalized linear mixed-effects model, with a Poisson distribution and a log link specified for count data with corrections for overdispersion, including a Vuong test for overdispersion and, where indicated, the use of a negative binomial model [69]. All analyses will include binary indicators of study arm allocation to assess for systematic differences in primary and secondary outcomes of interest across study arms. Multivariate analyses will be adjusted for: (1) binary indicators of the type of income assistance the participant receives; (2) an indicator variable for whether the individual changed their financial service provider to Pigeon Park Savings (PPS) at the start of the study to control for the effect of becoming a PPS client; (3) socio-demographic characteristics, including gender, ethnicity and age; indicators of addiction treatment enrollment and DTES residency, and (4) a categorical variable for the number of days between government cheque issue and their study visit to account for differences in recall reliability. As is common in RCT analyses [70, 71], missing assessments of intensified drug use will be treated as positive and tested for sensitivity to this assumption [72, 73]. Additional sensitivity analyses will include: (1) a modified intention-to-treat analysis using all participants with at least one follow-up assessment [74]; and (2) per-protocol analyses of participants who maintain enrollment in the intervention [75, 76].

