There are potentially important differences between the two interventions that may affect their relative efficacy. For example, staggering social assistance payments could displace consumption for individuals away from government cheque issue, but may not reduce overall consumption. At scale, this may improve experiences of service providers who would not have to manage cyclical escalations in service demand, but may provide little benefit to individual PWUD other than improved service access. Staggering and splitting income assistance payments may support smoothing consumption patterns, but may potentially result in multiple periods of escalated drug use signaled by more than one monthly payment. The testing of two different payment schedules enables us to examine which approach, if either, more effectively decreases spikes in drug use and drug-related harm coinciding with synchronized social assistance disbursement.

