### Objectives

The main objective of TASA Cheque issue study is to assess the effectiveness of structural changes in the timing and frequency of social assistance payments in reducing drug use and drug-related harm in the days surrounding social assistance cheque issue in a population of socio-economically marginalized people who use illicit drugs. The interventions will be compared with each other and with a no-intervention control group.

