### Measures

Table 1 outlines the measures taken at screening, baseline, follow-up, withdrawal and study exit interviews and through post-study data linkages. For all primary and secondary outcomes of interest described below, we collect data on indicators on government cheque issue days by tracking activity and exposures on a daily basis or through specific questionnaire items and response options. Where government cheque issue and individual cheque issue timing are not the same (i.e., for intervention participants), we additionally ask specific questions about individual cheque issue day activities and exposures. By collecting information about the occurrence of key outcomes of interest on non-cheque issue days as well as those coinciding with government and individual payments, we are better able to distinguish between individual cues for increased drug use coinciding with individual payments and social cues prompted by synchronized payment across the population on government cheque issue day.

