#### Health service utilization

Several key secondary outcomes of the TASA study are linked to whether the study intervention can reduce or smooth health service utilization. Previously identified health service impacts of synchronized social assistance include ED, EDMH or SUH admissions [7, 11–13, 19, 57]; discharges against medical advice directly prior to cheque issue [7, 9, 12]; health service access barriers linked to elevated demand [6]; and interruptions to ongoing medical care [9, 22]. In support of these assessments the study instrument collects past six months (baseline) and past 2 weeks (baseline and follow-up) information on which health services were accessed, whether participants attempted but were unable to access a service, the timing and reason for encountering service access barriers and whether participants missed medical appointments around cheque issue. We additionally collect information on whether, if hospitalized, participants left hospital against medical advice, as well as the reasons for and timing of their departure.

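### ED admissions, and any other outcome analysed as a whole-period count, can show a change in total service use but not smoothing or a fall around government cheque issue

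*Protocol article*

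**What the plan says.** The Quantitative analyses section describes two groups of secondary outcomes.

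- The first is handled like the primary outcome, a repeated binary tied to each government cheque issue: "This outcome, and other secondary outcomes similarly quantified will be examined using pooled generalized linear mixed effects models". Its members are not listed.
- The second is a count group: "Other secondary outcomes of interest, quantified as counts of the number of occurrences over the course of the observation period". Hospital ED admissions are the only example given. These use a Poisson or negative binomial mixed model.

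For both groups, "All analyses will include binary indicators of study arm allocation to assess for systematic differences in primary and secondary outcomes of interest across study arms". The adjusted models add assistance type, change of financial provider, socio-demographic and treatment indicators, and the number of days from government cheque issue to the study visit. None of these describes when an event happened.

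Elsewhere the article asks about timing:

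- Objectives: the aim concerns "reducing drug use and drug-related harm in the days surrounding social assistance cheque issue".
- Health service utilization: several key secondary outcomes turn on "whether the study intervention can reduce or smooth health service utilization".
- Background: staggering "could displace consumption for individuals away from government cheque issue, but may not reduce overall consumption". The benefit described for providers is relief from cyclical peaks in demand. The Background also reports that delayed payments were followed by matching delays in drug-related hospitalization.
- Measures: cheque-day data are collected for all primary and secondary outcomes so that the investigators are "better able to distinguish between individual cues for increased drug use coinciding with individual payments and social cues prompted by synchronized payment".
- Discussion: linked records are meant to show whether either intervention eases service problems around government cheque issue.

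**The concern.** A count over the whole period takes the same value whether the events cluster on government cheque days, on the participant's own payday, or nowhere. The article gives the primary outcome a cheque-day window but gives ED admissions none. Followed as written, the plan leaves the smoothing question untested for ED admissions, although the Measures section says data suited to it are collected. A null result on the total could then be misread as no effect on cheque-related service demand, when demand had in fact been spread out. Two smaller peaks under split payments would be equally invisible.

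**Working it through.** **The plan's own figures.** The article gives no effect size or power for the count outcomes. Its 65 and 91 per arm belong to the primary outcome. They reproduce if the 20% difference is read as relative (85% vs 68%). The pooled two-proportion formula gives 96.5 per arm. Then 96.5 × [1 + 5 × 0.6]/6 = 64.3, so 65. With four of six measures kept, 96.5 × [1 + 3 × 0.6]/4 = 67.5, and 67.5/0.75 = 90.03, so 91. This point does not affect them.

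**Inputs.** From Sample size: excess harm e = 0.249 to 0.812 around cheque issue. From the primary outcome definition: a 3-day window. Assumed: the whole excess falls in that window, the rate is flat on other days, and a cycle has D = 30.4 days.

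**Effect on the total and in the window**, with one unit of events per ordinary day:

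- Control events per cycle: D + 3e = 31.147 (e = 0.249) or 32.836 (e = 0.812).
- Share falling in the window: 3(1 + e)/(D + 3e) = 3.747/31.147 = 12.0%, or 5.436/32.836 = 16.6%.
- Fall in the total if the excess is removed: 3e/(D + 3e) = 0.747/31.147 = 2.4%, or 2.436/32.836 = 7.4%.
- Fall in the window rate: 1 − 1/1.249 = 20%, or 1 − 1/1.812 = 45%.
- If the excess is only displaced, the window rate falls by the same 20 to 45% and the total changes by 0%.

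**Sensitivity.** For D from 28 to 35 days, the fall in the total runs from 2.1% (D = 35, e = 0.249) to 8.0% (D = 28, e = 0.812). If the excess covers 7 days, the fall is 7 × 0.249/(30.4 + 1.743) = 5.4% to 7 × 0.812/(30.4 + 5.684) = 15.8%. The window length therefore matters, but displacement still gives 0%.

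**Power.** The documents give no ED rate. Assumed: m = 0.5 to 3 admissions per control participant over six months, 91 per arm with no losses, and negative binomial dispersion k = 0 or 1. The Wald standard error of the log rate ratio is √[1/(91m) + 1/(91m·RR) + 2k/91]; for the window, m is multiplied by the window share. With the excess fully removed and D = 30.4:

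| Comparison of arms | Rate ratio | Power |
|---|---|---|
| Whole-period count | 0.976 to 0.926 | about 5 to 14% |
| Count in the 3-day window | 0.80 to 0.55 | about 6 to 66% |

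Control-arm events in the window would number about 91 × 0.5 × 0.120 = 5 to 91 × 3 × 0.166 = 45.

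**The case against.** Several points on the other side stand.

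- **Totals answer a real question.** The stated aim is to reduce or smooth, and a total tests the first. Study design lists ED admissions among the secondary outcomes without a cheque-day qualifier. Under pure displacement, a null total is the correct answer about individual burden.
- **Scope.** A reader might infer that overdose, violence, police contact and the other harms are all counted this way. The text does not support that. Only ED admissions are named, and other outcomes may sit in the cheque-window binary group.
- **Displacement.** A reader might infer that the trial expects displacement. The Background says only that it could happen, and speaks there of consumption. It also raises smoothing and repeated peaks. The reported delays in hospitalization make displacement plausible for service use, but do not make it the trial's prediction.
- **Model detail.** The adjusted models do contain covariates. A mixed model could also use repeated counts per person, so a single total per participant is not certain. Without a timing term, either form estimates an average rate.
- **Condensed article.** These are secondary outcomes of a trial labelled exploratory, and allocating each outcome to a group may be left to a fuller document. That would answer a complaint about missing detail. Here, however, the article states a form for ED admissions, and that form cannot address part of the stated aim.

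**Conclusion.** The point holds for ED admissions, and for any other outcome that stays in the count group. The whole-period count is incomplete, not wrong: it measures total burden but carries no information on smoothing or on the days around government cheque issue. Under the 3-day, 30.4-day assumption, abolishing the cheque-day excess moves the total by about 2.4 to 7.4% against 20 to 45% in the window; displacement moves the total by nothing. These sizes rest on placing the article's pooled range of harms in one short window, and a longer window raises the fall in the total. The power figures rest on assumed ED rates. It would go too far to say that the trial will conclude there is no effect on service use, because the article states no such decision rule. The primary analysis and the sample size are untouched. The change should be made because it is cheap and the risk of misreading is real.

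**What to change.** 1. State which secondary outcomes are cheque-window binaries and which are counts.
2. Keep the whole-period count as the measure of total burden.
3. For ED admissions and any other dated outcome in the count group, add a companion analysis. Split each participant's follow-up into government cheque window and other days. Model the counts with log(days) as offset, arm, window and arm-by-window terms, and the planned covariates and random effect. Report the arm rate ratio in the window, and the window-to-other-days rate ratio by arm as the measure of smoothing.
4. Analyse own-payday windows as a separate contrast. In controls own payday coincides with government cheque day, so a separate own-payday category would be empty in that arm.
5. For discharges against medical advice, use a window before cheque issue, because the Health service utilization section places them directly before it. A window starting on cheque day would miss them.
6. Fix the window lengths before the data are examined.

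The cost is analysis wording and programming. It assumes that the requested hospital and police records carry event dates; the questionnaire also collects cheque-day information. The downside is precision: only about 12 to 17% of events would fall in a 3-day window, so intervals will be wide and power may stay low. The results should be reported as estimates with intervals, and a null window result should not be read as evidence of no effect.

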### Follow-up assessments

Once individuals enrol (control arm) or receive their first payment on their individual schedule (staggered and staggered and split) arms, follow-up visits occur every 2 weeks for the 26-week period of active study participation, for a total of one baseline and 13 regular follow-up interviews. Frequent follow-up visits mitigate recall-related threats to data reliability for key measures [38]. During study follow-up visits, a trained interviewer administers the follow-up questionnaire, which includes past 2 week assessments of all study measures. Participant safety, including the monitoring of adverse events or serious adverse events related and unrelated to study participation is also assessed at every follow-up. Follow-up visits take 20–30 min. Due to the intent-to-treat nature of the study, participants can withdraw from the intervention but are encouraged to continue to complete regular follow-up visits.

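### The protocol uses a Vuong test to decide whether the secondary count outcomes need a negative binomial model, but it is not a test of overdispersion and often misses a moderate excess of variance

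*Protocol article*

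**What the plan says.** The Quantitative analyses section of the protocol article divides the secondary outcomes in two. Some are repeated binary variables and share the primary outcome's logistic mixed model. The others are "quantified as counts of the number of occurrences over the course of the observation period", with emergency department admissions as the example, and these "will be examined using generalized linear mixed-effects model, with a Poisson distribution and a log link specified for count data". The same sentence continues: "with corrections for overdispersion, including a Vuong test for overdispersion and, where indicated, the use of a negative binomial model".

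The text therefore starts from Poisson, names one test for overdispersion, and moves to the negative binomial if overdispersion is indicated. It does not state the critical value or which two models the Vuong statistic compares. No other test of dispersion is named.

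**The concern.** The Vuong statistic asks which of two competing models fits better. In count regression it is typically used to compare an ordinary with a zero-inflated model. Overdispersion is a different question: is the negative binomial dispersion parameter k above zero? Poisson is the negative binomial with k = 0, at the edge of the parameter space. When one model is nested in the other in this way, the Vuong statistic does not have its standard normal reference. In practice the gate is very conservative.

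If the gate stays shut when the counts are overdispersed, the Poisson standard errors are too small and the confidence intervals for the arm comparisons too narrow. This would affect whichever secondary harm and service-use outcomes are analysed as counts. The article names hospital emergency department admissions. This is an error in a step that the article itself fixes, not a detail left for the analysis plan.

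**Working it through.** The protocol gives no figure for the count outcomes (expected mean, variance or power), so there is none to reproduce. The check asks how the stated rule behaves.

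**Inputs from the document.** 91 participants per arm (Sample size); Poisson first, then the Vuong test, then the negative binomial where indicated (Quantitative analyses).

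**Assumed inputs.** Mean count μ and dispersion k, with variance/mean = 1 + kμ; two arms with no true difference; one count per participant; no random effect; the gate opens when the Vuong statistic exceeds 1.96.

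**Formulas.** Let d be the difference in log-likelihood contribution (negative binomial minus Poisson) for each of N = 182 participants.
- Vuong: V = √N × mean(d) / SD(d), referred to a standard normal.
- Boundary likelihood-ratio test: 2 × Σd, compared with 2.706. This is the 5% point when half of the null distribution sits at zero.
- If Poisson is wrongly kept, the true standard error is √(1 + kμ) times the reported one. For μ = 1 and k = 0.5 this is √1.5 = 1.22.

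**Moderate overdispersion (4,000 runs per row).**

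| μ | k | Variance/mean | Vuong picks NB | Boundary LR picks NB | Type I error, Vuong gate | Type I error, NB throughout |
|---|---|---|---|---|---|---|
| 1 | 0.5 | 1.5 | 23% | 96% | 9.2% | 5.2% |
| 0.5 | 1 | 1.5 | 17% | 93% | 9.2% | 5.5% |
| 0.3 | 2 | 1.6 | 18% | 94% | 9.1% | 5.0% |

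The 95% Monte Carlo error on a 9% rate is about 1.96 × √(0.09 × 0.91 / 4,000) = 0.9 percentage points. A separate set of 2,000 runs per scenario gave 16–23% for Vuong, 92–95% for the likelihood-ratio test, and errors of about 9% and 5%.

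**Larger overdispersion (2,000 runs per scenario, Vuong gate).**

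| Variance/mean | Vuong picks NB | Type I error at μ = 2, 1, 0.5 |
|---|---|---|
| 2 | 66–94% | 5.0%, 7.2%, 9.0% |
| 3 | 93–100% | 5.2%, 5.5%, 7.3% |

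**No overdispersion.** The Vuong gate never chose the negative binomial. The negative binomial used throughout had a type I error of 4.1%, so it costs nothing in error control.

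**Alternative reading of the gate.** If the Vuong test instead compares Poisson with zero-inflated Poisson, it does no better as a check on dispersion. In 400 runs per scenario it rejected Poisson in 16% at μ = 1, k = 0.5 and in 76% at μ = 1, k = 1. The boundary likelihood-ratio test rejected in 97% and 100%.

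**The case against.** The strongest defence is that the plan does take overdispersion seriously. It promises corrections, of which the Vuong test is only one stated part, and it names the negative binomial as a fallback. It also specifies a mixed model, and a participant random effect absorbs extra-Poisson variation, which the simulations leave out. Large overdispersion is caught in most runs. The outcomes are secondary, in a trial that describes itself as exploratory; the primary outcome, its model and the sample size are untouched.

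Most of this stands, and it limits the size of the problem. It does not rescue the step. The Vuong test is the only dispersion test named, and it is described as doing something that it does not do. A pre-specified fallback is not in itself a fault: with a likelihood-ratio gate the simulated error stayed at 4–6%. The fault lies in this particular gate.

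A reader might also infer that the plan compares raw counts over unequal follow-up, so that an arm observed for less time looks safer. The document does not support that. It names no offset but rules none out, and an offset is a detail that an article commonly leaves to the analysis plan, which is not shown. Planned follow-up is the same in every arm: "follow-up visits occur every 2 weeks for the 26-week period of active study participation". Counts taken per visit would cover equal intervals. Linked hospital and police records do not depend on attendance: "Records will be requested for a 30-month period beginning 1 year before the beginning of active study participation". The loss to follow-up allowed for in the sample size is a single 25% with no difference by arm, and equal loss does not bias the comparison.

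**Conclusion.** The point holds, at modest size. As written, the rule that selects the count model rests on a test that does not address overdispersion and has no valid normal reference for Poisson against the negative binomial. With a variance about 1.5 to 1.6 times the mean and low mean counts, the gate misses the excess in roughly four runs out of five, and a nominal 5% test runs at about 9%.

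These figures depend on assumed means and dispersions, a cut-off of 1.96 and no random effect, so they are upper-end illustrations. A reader might take the error of a wholly uncorrected Poisson analysis as the plan's risk: 2 × (1 − Φ(1.96/√2)) = 17% at twice the mean and 2 × (1 − Φ(1.96/√3)) = 26% at three times. That goes too far. At those ratios the gate usually opens, and the simulated error is about 5–9%. Only secondary outcomes are affected. The correction is worth making because the step is wrong on its face and simple to replace.

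**What to change.** Delete the Vuong step and pre-specify a negative binomial model with log link for every count outcome, with Poisson as a sensitivity analysis. If a gate is preferred, replace the Vuong test with a boundary likelihood-ratio test or a score test of the dispersion parameter, and state its critical value. A Vuong comparison should be kept only if a zero-inflated model is a genuine candidate, and should then be described as a comparison of models.

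The cost is a change of wording before analysis, and slightly wider intervals if the counts prove not to be overdispersed. Data collection, sample size and the primary analysis do not change.
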